#### Statistical methods

Statistical analysis will be carried out after all patients have completed 12 months of follow-up. Fisher’s exact test will be used for the primary endpoint of the trial. In order to analyze secondary endpoints, the type of data distribution will be studied. If the results follow a normal distribution, the chi-square test and *t* test will be used to compare qualitative and quantitative parameters accordingly. If the results do not follow a normal distribution, quantitative parameters will be studied with the Mann-Whitney test. Depending on the data collected, further tests, such as the Wilcoxon and Kruskal-Wallis tests, may be done for subgroups. Statistical differences will be considered significant if *P* < 0.05.

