**Fig. 1 Fig1:**
[figure not shown]
Study flowchart

**Table 1 Tab1:** Standard Protocol Items: Recommendations for Interventional Trials (SPIRIT) diagram

	Study period					
	Enrollment	Allocation	Post allocation			
Time point	Preintervention	Time 0	Baseline (Intervention)	Post intervention	6-month follow-up	12-month follow-up
Enrollment:						
Eligibility screen	X					
Informed consent	X					
Allocation		X				
Interventions:						
Control group: repair of rotator cuff *only*			X			
Second group: repair of rotator cuff and SSN release			X			
Assessments:						
NC/EMG studies	X				X	X
Clinical shoulder assessment/signs	X			X	X	X
Constant-Murley score	X				X	X
DASH score	X				X	X
ASES score	X				X	X
MRI scan	X					X

*ASES* American Shoulder and Elbow Surgeons, *DASH* Disabilities of the Arm, Shoulder and Hand, *EMG* electromyography, *MRI* magnetic resonance imaging, *NC* nerve conduction, *SSN* suprascapular nerve

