As per the surgical protocol, all patients will also undergo tenotomy of the long head of biceps and acromioplasty with excision of the coracoacromial ligament. Also, excision of the acromioclavicular joint will be performed only if patients complain of pain in that region along with degenerative changes being shown on X-rays, or found intraoperatively. If any further lesions are detected during the operation, the surgeon will proceed to repair them and such incidents will also be recorded. Skin closure will be performed with 3.0 nylon sutures. Nonadhesive dressings and pressure dressings will be applied to the top of the shoulder and patients will be placed in a 30^o^ abduction sling immediately after completion of surgery.

Patients will stay overnight at the hospital. Physiotherapists will advise them as per the physiotherapeutic protocol (Table 2). The abduction sling will remain for the first 6 weeks. Sutures will be removed 10 days after surgery. Outpatient and physiotherapy clinic follow-up will be arranged at 6 weeks, 3 months, and 6 and 12 months postoperatively. Neurology clinics for NC/EMG studies will be arranged at 6 and 12 months postoperatively. Outcome scores will be collected at 6 and 12 months after surgery.

**Table 2 Tab2:** Brief physiotherapy protocol for postoperative rehabilitation of repaired large/massive rotator cuff tears

Time	Focus	Range of motion	Recommended exercises	Precautions
0–6 weeks	Tissue healing	No passive assisted or active ROM of shoulder allowed apart from table slides	• Restricted table slides after 2nd week to 30° • AROM of elbow, wrist, hand	• No active reaching • Sling at all times
6–12 weeks	PROM, AAROM with transition to AROM	Regain full PROM and AAROM, transition to AROM at 10 weeks	• PROM of shoulder, pendulums, scapular mobility, ball squeeze begin AAROM at 8 weeks • Isometrics and active progression at 10 weeks	• No resisted activity and lifting • Avoid overloading of supraspinatus • Must regain scapular rhythm before transition to strengthening
12–24 weeks	AROM and progressive strengthening	Regain full AROM	• Continue PROM and AAROM as needed • Initiate strengthening and progress AROM to functional planes • Progress proprioceptive drills, rhythmic stabilization, push-ups, resistance band	• No heavy or repetitive overhead activities • Limited return to gym after 20th week if AROM with satisfactory scapular rhythm has been achieved • Free full ROM

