### Statistics

#### Sample size calculation

Statistical analysis of previous relevant medical literature was used in order to identify the number of patients needed for this trial. Since no similar studies could be found, we searched for results from similar articles relative to the trial. Costouros et al. [7] treated six patients with massive rotator cuff tears and SSN neuropathy by arthroscopically repairing the cuff. They found complete nerve recovery in four out of six patients. Oizumi et al. [17] performed an arthroscopic release in 18 patients with a rotator cuff tear and all had complete recovery from SSN palsy, although the diagnosis was clinical and no NC/EMG studies were done. Lafosse et al. [1] mention unpublished data of 29 massive rotator cuff tear cases accompanied by SSN neuropathy, where no statistical difference was found between patients who underwent nerve release and patients who did not; however, no further data or tables are provided and the cases are anecdotal. Therefore, we considered that 100% of patients undergoing nerve release and 66.67% of patients undergoing rotator cuff repair only could have full nerve recovery.

We used the statistical program G*Power [18] in order to do a priori power analysis of the primary endpoint of this study. By using a Fisher’s exact test to compute differences between these groups, a 100% success probability of the first group (nerve release) and a 66.67% probability of the second group, a error probability set at 0.05, power set at 0.8, and an allocation ratio equal to 1, a total of 38 patients were found to be needed, 19 for each group. Usually, patients who undergo such operations rarely miss standard follow-ups in this institution because these are part of their physiotherapy and clinical postoperative care (apart from the NC/EMG studies). If 10% of recruited patients fail to attend follow-ups for any reason, then 42 patients will be required for this RCT.

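### Non-primary outcomes: the test is picked after a look at the distribution, none of the named tests takes a baseline covariate, and chi-square is tied to normality

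*Protocol article*

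**What the plan says.** The Statistical methods section gives the primary endpoint to Fisher's exact test. For the secondary endpoints it first inspects the distribution and then branches. The first branch opens "If the results follow a normal distribution, the chi-square test and" t test, for qualitative and quantitative parameters respectively. The second reads "If the results do not follow a normal distribution, quantitative parameters will be studied with the Mann-Whitney test" and names nothing for qualitative parameters. Wilcoxon and Kruskal-Wallis tests are left open as additions for subgroups. No adjusted model is named, and the section does not say whether follow-up values or changes from baseline are compared.

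Baseline values will exist. The SPIRIT diagram (Table 1) marks "Constant-Murley score", DASH, ASES, nerve conduction/EMG and MRI before the intervention. The section on preoperative and postoperative examinations adds range of motion and shoulder power. On follow-up, the Study procedure section says "Outcome scores will be collected at 6 and 12 months after surgery".

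**The concern.** The rule has three weaknesses.

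- **The data choose the comparison.** The t test compares means and Mann-Whitney compares ranks. Which one is reported for a given score is known only after the data have been inspected, and two scores in the same trial could end up with different kinds of result.
- **Baseline is collected but has no place in the named between-group tests.** With about 20 patients per arm, chance differences at baseline are common. A patient's preoperative value is usually informative about the later one, so leaving it out gives up precision that costs nothing to recover.
- **Chi-square hangs on a condition that cannot be met.** Qualitative data are not normally distributed; the validity of chi-square depends on expected counts. Read literally, the rule cannot be carried out for qualitative outcomes.

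At stake are the width of the confidence intervals for the functional scores and how clearly they can be interpreted.

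**Working it through.** **The plan's own figure.** The Sample size calculation section gives "a error probability set at 0.05, power set at 0.8, and an allocation ratio equal to 1", with "a 100% success probability of the first group (nerve release) and a 66.67% probability of the second group". Exact enumeration of Fisher's test gives power 0.769 at 18 per arm and 0.812 at 19 per arm, so "a total of 38 patients were found to be needed, 19 for each group" reproduces. On dropout the section says "If 10% of recruited patients fail to attend follow-ups for any reason, then 42 patients will be required for this RCT"; 38 × 1.1 = 41.8 gives 42, whereas 38 / 0.9 = 42.2 would round up to 43. These figures concern the primary endpoint only and are not affected by this point. They supply the 19 evaluable and 21 randomised patients per arm used below.

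**Precision.** The documents give no correlation r between baseline and follow-up, so r = 0.3, 0.5 and 0.7 is an assumed range. Take equal variance at both times and set the variance of a follow-up-only comparison to 1.

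- ANCOVA: 1 − r²
- Change score: 2(1 − r)
- ANCOVA relative to change score: (1 − r²) / [2(1 − r)] = (1 + r)/2

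| Assumed r | ANCOVA vs follow-up only | Change score vs follow-up only | ANCOVA vs change score |
|---|---|---|---|
| 0.3 | 0.91 | 1.40 | 0.65 |
| 0.5 | 0.75 | 1.00 | 0.75 |
| 0.7 | 0.51 | 0.60 | 0.85 |

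ANCOVA has the smaller variance against either comparator in every row.

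**What this means at 19 per arm** (two-sided 5%, noncentral t, one degree of freedom spent on the covariate):

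| | No covariate | r = 0.3 | r = 0.5 | r = 0.7 |
|---|---|---|---|---|
| Difference detectable at 80% power (SD) | 0.934 | 0.892 | 0.810 | 0.668 |
| Power at 0.934 SD | 80% | 83.5% | 89.8% | 97.5% |
| Equivalent unadjusted total, 38/(1 − r²) | 38 | 41.8 | 50.7 | 74.5 |

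At 21 per arm the detectable difference falls from 0.886 SD to 0.846, 0.768 and 0.633 SD.

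**Baseline imbalance.** With 21 per arm, the standard error of the difference in baseline means is √(2/21) = 0.31 SD. A chance difference above 0.3 SD in either direction corresponds to |Z| > 0.3/0.31 ≈ 0.97, which happens in about one trial in three for each measure. A follow-up-only comparison carries this into the estimate in proportion to r.

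**The normality gate.** In 8,000 simulated null trials with 19 per arm, a Shapiro-Wilk check in each arm at 5% chose between the t test and Mann-Whitney. Type I error of the two-step procedure was 4.8% for normal data, 4.9% for lognormal and 4.4% for exponential. About 10% of the trials with truly normal data were sent to Mann-Whitney. Shapiro-Wilk is an assumption here, because the article names no formal check.

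**Chi-square.** Reading the two branches together, the qualitative parameters appear only under the normal branch, and the other branch is restricted to quantitative ones. Qualitative outcomes therefore have no test whenever the results are judged non-normal.

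**The case against.** The strongest reply is about scope. This is a journal article and a separate analysis plan may exist, so covariate adjustment and ordinal modelling could be set out there. An unadjusted comparison in a randomised trial is also valid and unbiased. Both statements are true. However, the article is not silent here: it fixes a decision rule and names the tests, and that stated rule is what is at issue. Choosing ANCOVA over it is a gain in efficiency, not the repair of a bias.

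The chi-square wording may be only a drafting slip, since the sentence pairs each test with its type of parameter. That is plausible, and it makes the correction easy, but the text as it stands still leaves a gap.

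Four stronger readings are tempting and are not supported:

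- **That the normality gate raises the false-positive rate or makes the choice close to arbitrary.** The simulation shows no inflation (4.4% to 4.9%) and only about one normal trial in ten switched.
- **That the plan ignores baseline altogether.** The article does not say whether follow-up values or changes are analysed, and the section on objectives and endpoints speaks of changes in places. A test on change scores does use baseline, though less efficiently than ANCOVA at each r tried.
- **That the planned recovery rates show chi-square tables will be too sparse.** Those rates belong to the primary endpoint, which goes to Fisher's test. The documents give no event rate for any other qualitative outcome.
- **That the shoulder scores are declared secondary endpoints.** The article defines the secondary endpoint as relations between tear size, neuropathy and recovery, and the tertiary endpoint as change in Goutallier stage. The scores are collected without a label. The rule is the only one stated that could cover them, but that is a reading. None of the named tests estimates a correlation with tear size either, which is a separate gap.

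**Conclusion.** The point holds for the non-primary outcomes. The dependence of the test on the observed distribution, and the condition placed on chi-square, are both in the text. The loss of precision follows from the tests named, none of which takes a baseline covariate.

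Its size rests on an assumed correlation. Against a follow-up-only comparison the gain is small at r = 0.3 (9% of the variance) and large at r = 0.7 (49%). Against a change-score comparison the order reverses, with gains of 35% at r = 0.3 and 15% at r = 0.7. The article does not say which comparator applies, but ANCOVA does better than both throughout the range.

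This is worth correcting but does not threaten the trial's main result.

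**What to change.** Rewrite the paragraph on non-primary outcomes as follows.

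- Remove the normality check as the switch between tests.
- Compare Constant-Murley, DASH, ASES and the other quantitative outcomes at 12 months, and at 6 months, by ANCOVA with arm and the patient's own baseline value. Report the adjusted difference with its 95% confidence interval, and add a rank-based sensitivity analysis.
- Use Fisher's exact test for qualitative outcomes whatever the distribution of the other data, as the plan already does for the primary endpoint.
- Analyse Goutallier stage by an ordinal or rank method that takes account of the baseline stage.

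The cost is one paragraph of text. No new data are needed, since every baseline value is already scheduled. The article describes the trial as still recruiting and defers analysis until all patients have completed 12 months, so the change can be made before outcomes are analysed.

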#### Randomization/blinding

The choice of resecting or not the transverse scapular ligament will be done in a randomized manner. Randomization will be made by using the Microsoft Office Excel program and its RAND function. Forty-two cells will be created and the numbers in them will be rounded up so that they have no decimals. Odd numbers will create the first group and even numbers will create the second group. If RAND function fails to create even groups, it will be redone until even groups of odd and even numbers are achieved. Patients will be placed at each consecutive cell at the time of recruitment, after inclusion in this trial, and will be randomized by the statistician. The surgeon will be informed about the type of treatment needed for patients on the admission day. This will be facilitated with opaque envelopes containing the patient’s group, which the primary investigator will have received from the statistician. The primary investigator will place this envelope inside the patient’s physical records just before the patient is taken to the operating room. An operating department practitioner nurse will open the envelope just after the surgeon finishes the rotator cuff repair and will instruct him, according to the patient’s group, whether to release the ligament or not. By doing this, the surgeon will not be biased by knowing the patient’s group before repairing the cuff (avoidance of performance bias).

The surgeon, therefore, clearly cannot be blinded to the type of procedure, but this will not bring any bias to the study. Patients, physiotherapists, and the clinician measuring outcomes will be blinded to each patient’s allocated treatment. The neurologist will also not know the type of surgery performed. This blinding will assist in obtaining objective results while performing NC/EMG studies and should exclude such bias.

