### Study population

Forty-two patients with SSN neuropathy and repairable large or massive rotator cuff tears will be recruited according to the inclusion/exclusion criteria of this RCT, divided in two equally numbered groups and treated within a 24-month period at the First Orthopedic Department of Aristotle University of Thessaloniki, “Georgios Papanikolaou” Hospital, Greece. Inclusion criteria are: patients with large or massive repairable rotator cuff tears combined with SSN neuropathy on the ipsilateral side. Exclusion criteria are: SSN neuropathy of another cause (e.g., brachial plexus neuropathy), other previous surgery performed on the same affected shoulder, and moderate to severe degenerative changes to the ipsilateral glenohumeral joint (rotator cuff arthropathy).

All patients seen in our institution’s shoulder clinic with MRI-confirmed large or massive repairable rotator cuff tears and suspected SSN neuropathy will undergo NC/EMG studies in order to establish a diagnosis of the neuropathy. Patients with no signs of pain, atrophy, or paresthesia over the SSN distribution area, or patients who refuse to have any more diagnostic processes, will not have NC/EMG studies and will not be considered for the study. If the above studies are positive for SSN neuropathy, and the patients meet the inclusion and none of the exclusion criteria, they will be informed about this trial. If they agree to participate in this trial and sign and date the informed consent, then a further preoperative appointment will be given.

An investigator will clinically examine the patients on the second preoperative appointment. A specific form will be created for each one that will contain demographic, preoperative, and postoperative data (Additional file 2: Table S1). All patient forms will additionally be kept in electronic records for easier data analysis. Randomization and allocation of patients to a specific group will be done by the statistician. All patients, the clinical preoperative and follow-up examiner, and the neurologist performing the NC/EMG studies will be blinded to the type of surgery performed.

The first group of this trial will be the control group and will consist of 21 patients; these will undergo arthroscopic repair of the rotator cuff tear. The second group will also consist of 21 patients. They will undergo the procedure as above, along with an arthroscopic release of the SSN at the same stage.

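### The published randomisation rule cannot produce a 21/21 list: RAND values rounded up are all 1, so every patient falls in the first (control) group

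*Protocol article*

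**What the plan says.** The rule is in the Randomization/blinding section of the protocol article, in four steps.

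- Source: "Randomization will be made by using the Microsoft Office Excel program and its RAND function".
- Transformation: "Forty-two cells will be created and the numbers in them will be rounded up so that they have no decimals".
- Assignment: "Odd numbers will create the first group and even numbers will create the second group".
- Stopping rule: "If RAND function fails to create even groups, it will be redone until even groups of odd and even numbers are achieved".

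No multiplier, range or other generating formula is given there or elsewhere in the article. Patients take the cells in order as they are recruited, and the statistician does the randomising.

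The Study population section fixes the target and the meaning of the groups: "The first group of this trial will be the control group and will consist of 21 patients", and "The second group will also consist of 21 patients". The abstract and Table 1 agree that control comes first and release second. The Sample size calculation section uses the opposite label: "a 100% success probability of the first group (nerve release".

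**The concern.** The article could have left sequence generation to the full protocol. Instead it states a complete algorithm, and the steps do not fit together. A function that returns values between 0 and 1, followed by rounding up, gives a constant. A constant has one parity, so an odd/even split puts everyone in the same arm and the condition for accepting the list is not met.

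Randomisation is the only basis for comparing the two arms with Fisher's exact test in this single-center trial of 42 patients. A reader who checks how the sequence was made will find a rule that yields one arm. Whatever was done to obtain 21 and 21 must differ from the published text, so the allocation cannot be reproduced or audited from it.

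**Working it through.** **Inputs.** 42 cells, RAND, rounding up, odd/even assignment and redrawing until equal (Randomization/blinding); 21 per group (Study population). Assumption, not stated in the article: RAND is uniform on [0,1).

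**The plan's own figure.** The number of cells comes from the sample size. The inputs are 100% against 66.67% recovery and "a error probability set at 0.05, power set at 0.8, and an allocation ratio equal to 1". Enumerating both binomials, the power of Fisher's exact test is 0.769 at 18 per group and 0.812 at 19 per group, the same one- and two-sided. This reproduces 19 per group and 38 in total. Adding 10% gives 38 × 1.10 = 41.8, rounded to 42. (Dividing instead, 38 / 0.90 = 42.2, would give 43; the present point does not depend on this.) The number of cells is therefore as the article says, and the problem lies only in how they are filled.

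**The rule as written.**

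1. For any x with 0 < x < 1, rounding up to an integer gives 1.
2. 1 is odd, so the cell goes to the first group.
3. This holds in all 42 cells, so the split is 42 odd / 0 even.
4. Equal groups require 21 even values, and the only even value available is 0, which needs RAND to return exactly 0. If RAND had a grid as coarse as 2⁻¹⁵, the probability of 21 zeros in 42 cells would be about C(42,21) × (2⁻¹⁵)²¹ ≈ 8 × 10⁻⁸⁴. A finer grid makes it smaller still.

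Simulation agrees: in 200,000 lists of 42 values the only rounded-up value was 1, every list was 42/0, and none was 21/21.

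**Two nearby rules that would work.**

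- *Rounding to the nearest integer.* Values are 0 or 1, each with probability 0.5.
- *Scaling by an even number k before rounding up.* Odd and even again each have probability 0.5. The simulated share of odd values was 0.500 for k = 2, 10, 42 and 100.

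Under either rule the chance that one draw splits 21/21 is C(42,21) / 2⁴² = 538,257,874,440 / 4,398,046,511,104 = 0.1224. The expected number of draws is 1 / 0.1224 = 8.17, so the repeat step ends.

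**Does redrawing introduce bias?** With parity probability 0.5, each specific list has probability 2⁻⁴². Conditional on a 21/21 split, each of the C(42,21) balanced lists therefore has the same probability, 1 / C(42,21). That is exactly the distribution of one random permutation of 21 and 21 labels. The 0.1224 and 8.17 describe only how long the procedure takes.

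**The case against.** The strongest reply is that this is a slip in a condensed description. The repeat step makes sense only if the authors saw both odd and even numbers, so they probably scaled RAND, or wrote rounding up where they meant ordinary rounding. Either would give a valid list. The range of RAND is also outside knowledge, which is why it is given here as an assumption. All of this stands, and it limits what can be concluded. It does not rescue the sentence, which states a specific operation that gives the wrong result.

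Four stronger readings are tempting, and the article does not support them.

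- *The list in use is invalid, or no proper list exists.* The text cannot show this. The statistician makes the allocation, and opaque envelopes carry it to theatre, where they are opened only after the cuff repair.
- *Redrawing until balanced allows selection.* The stopping rule determines which draw is kept, namely the balanced one, and the resulting distribution is that of a permutation.
- *The list changes as patients are entered, because RAND recalculates.* The article does not say that live formulas stay in the sheet or that patients are typed into it. Taking the next cell can equally mean the next line of a finished list.
- *It is unclear which arm odd numbers receive.* The abstract, Table 1 and the Study population section all make control the first group. The opposite label in the Sample size calculation describes an input to the power program, names the arm in parentheses, and assigns nobody. It is a labelling slip.

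**Conclusion.** The rule is wrong as written. Assuming RAND is uniform on [0,1), it sends all 42 patients to the first (control) group, and the redraw step does not end with any probability worth counting. The published rule cannot have generated a 21/21 list, so the method actually used is undocumented in this article.

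The conclusion goes no further. It concerns the description of the procedure, and it is not evidence that the allocation was biased or that any patient was wrongly assigned. Sample size, endpoints and the planned test are unaffected. It still needs correcting, because sequence generation must be traceable and the correction is cheap while the trial is recruiting.

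**What to change.** Replace the sentence with a rule that works, in one of two ways:

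- State the exact formula actually used (the multiplier or the type of rounding), and that the list was fixed and dated before enrolment.
- Or specify one random permutation of 21 control and 21 release labels: for example, save 42 RAND values as fixed values, rank them, and give the lowest 21 one named arm.

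Because recruitment is under way, first establish how the existing list was made.

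- If it is shown to be a fixed random 21/21 list, keep it and correct only the text.
- Only if that cannot be shown, generate the unassigned places by one documented permutation of the labels remaining in each arm. With *a* patients already assigned to control and *b* to release, permute 21 − *a* control and 21 − *b* release labels over the remaining 42 − *a* − *b* places. A fresh 21 + 21 permutation would not fit a partly used list.

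Name the arms *control* and *release* throughout, and correct the first-group label in the Sample size calculation section.

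The cost is under an hour of the statistician's time and one paragraph of protocol text, with no change to sample size, endpoints or clinical care.

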### Study procedure

Patients will be randomized on the admission day and allocated to a group, so that they may undergo arthroscopic rotator cuff repair alone, or combined with arthroscopic release of the SSN. Only the operating surgeon, who will be the same for all patients, will be aware of the randomization results and patient allocation list.

All patients are going to be treated according to the established institutional protocol and the operation will follow well-defined standards in order to minimize adverse factors. All operations will be done with the patient in a beach-chair position, under general anesthesia and with a regional (interscalene) anesthetic block for postoperative analgesia. If general anesthesia is contraindicated, then the procedure will be done with the patient awake or mildly sedated and with the regional block as the main anesthetic agent; these patients will be recorded. Prepping will be done as per hospital protocol with aqueous povidone iodine 7.5%, and draping will be the same for all patients. Standard portals will be made for all patients: posterior, anterior, lateral, and anterolateral; a superior portal will additionally be made for patients undergoing release of the superior transverse scapular ligament.

The procedure will aim at fully restoring the rotator cuff to its anatomical footprint. When the cuff is not repairable then these patients will be excluded from the study. If during the operation the surgeon fails to fully repair the cuff and achieves only a partial repair, these patients will be recorded and followed up but separated from the cohort; their outcomes will be compared with those of the rest. All repairs will be done using a transosseous equivalent technique with peek anchors, knotted medially and knotless laterally. Arthroscopic release will follow the technique published by Lafosse et al. [1]. Visualization will be done mostly by the lateral portal and the shaver will mostly work through a lateral-anterolateral portal. The transverse ligament will be dissected via a superior portal, which is created under direct vision and uses a needle to identify the exact location of the portal.

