### Subject withdrawal

Patients may withdraw from the study at several stages of the trial, if they wish it, even after having signed the Consent Form. They may also reject an intervention or reject a follow-up evaluation. If patients reject the operation, then they will be excluded from the study. If they reject a follow-up evaluation, then their data will be analyzed and individually reported at the final report of this trial, irrespective of their group. During surgery, if moderate or severe rotator cuff arthropathy is found, or if the surgeon fails to repair the cuff or release the SSN, then patients will be withdrawn from the trial. Postoperatively, patients may be removed from the RCT if they deteriorate and a diagnosis of rotator cuff re-rupture is made by ultrasound or MRI studies.

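### The plan gives two different randomisation times, both before refusals and intraoperative exclusions are known, although the arm is needed only when the envelope is opened after the repair

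*Protocol article*

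**What the plan says.** **When a patient is randomised.** Protocol article, Randomization/blinding: a list of 42 cells is redrawn until odd and even numbers are equal in count, and then "Patients will be placed at each consecutive cell at the time of recruitment, after inclusion in this trial, and will be randomized by the statistician". Study procedure: "Patients will be randomized on the admission day and allocated to a group". Table 1 places allocation at Time 0, after enrolment, and ties it to neither event. According to Trial duration, the trial period starts 6 weeks before surgery, so recruitment and admission can be weeks apart.

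**When the arm is needed.** Randomization/blinding: "An operating department practitioner nurse will open the envelope just after the surgeon finishes the rotator cuff repair". The two operations differ only from that point on.

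**Who is removed after taking a cell.** Subject withdrawal: "If patients reject the operation, then they will be excluded from the study". The same section withdraws patients whose exclusion becomes apparent on the table ("During surgery, if moderate or severe rotator cuff arthropathy is found"), or in whom the repair or the release fails. Study procedure excludes irreparable cuffs and keeps partially repaired patients apart from the cohort.

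**What total is expected.** Study population plans 21 operated patients per group. Trial duration ends the trial when 42 patients have completed it. Under Sample size calculation, "a total of 38 patients were found to be needed, 19 for each group", raised to 42 in case 10% do not attend follow-up.

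**The concern.** The two sections count some patients differently. Someone who refuses between recruitment and admission is a randomised loss under one section and was never randomised under the other. The article promises CONSORT reporting, which needs a single randomised denominator.

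Under both timings, the cell is also assigned before the patient has gone through with surgery and before eligibility and repair are settled. The plan then removes patients for events that, apart from a failed release, are known before the envelope is opened. Its own envelope step makes these post-randomisation exclusions unnecessary. The list is fixed at 42, there is no stated rule for reusing a vacated cell, and the margin above the required number is only 42 − 38 = 4 patients. Each such exclusion can therefore reduce the analysed groups and move them away from 21/21.

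**Working it through.** **1. Order of events**

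| Event | Known before the envelope is opened? | Holds a cell (recruitment timing) | Holds a cell (admission timing) |
|---|---|---|---|
| Refusal between recruitment and admission | yes | yes | no |
| Refusal after admission-day randomisation | yes | yes | yes |
| Arthropathy found at surgery | yes | yes | yes |
| Irreparable cuff, failed or partial repair | yes | yes | yes |
| Failed release, later re-rupture | no | yes | yes |

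Randomising at envelope opening would keep the first four rows off the list. It does nothing for the last.

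**2. Reproducing the plan's sample size**

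Inputs from Sample size calculation: full recovery in 100% with release against 66.67% with repair alone, and "a error probability set at 0.05, power set at 0.8, and an allocation ratio equal to 1". Sidedness is not stated; two-sided is used here.

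With 100% recovery after release, power is the probability that the number of control failures, distributed Binomial(n, 1/3), reaches the smallest number giving P < 0.05.

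- At 19 per group, 4 failures give a one-sided P of C(19,4)/C(38,4) = 3,876/73,815 = 0.0525, which is not significant.
- 5 failures give a two-sided P of 2 × C(19,5)/C(38,5) = 2 × 11,628/501,942 = 0.0463, which is significant.
- Power is therefore P(Binomial(19, 1/3) ≥ 5) = 0.812. At 18 per group it is 0.769.

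So 19 per group, 38 in all, is confirmed. The one-sided test gives the same power at these sizes.

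**3. Balance after k exclusions**

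The article gives no exclusion rate, so k is an assumption. If k cells are lost at random from 21/21, the chance that x come from one group is C(21,x) × C(21,k−x)/C(42,k).

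- k = 2: the groups stay equal with probability 21 × 21/861 = 0.51.
- k = 4: 210 × 210/111,930 = 0.39.
- Any odd k: zero.

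Even an equal split leaves fewer than 21 per group.

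**4. Power after exclusions and missed follow-up**

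Fisher power was averaged over all random splits of the total number lost. Four missed follow-ups is the plan's 10% of 42, rounded.

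| Assumed exclusions | Missed follow-ups | Evaluable | Mean power |
|---|---|---|---|
| 0 | 4 | 38 | 0.843 |
| 2 | 4 | 36 | 0.803 |
| 4 | 4 | 34 | 0.757 |
| 2 | 0 | 40 | 0.874 |
| 4 | 0 | 38 | 0.843 |

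The mean at 38 exceeds the 0.812 for 19/19 because the test is discrete. With 20 release and 18 control patients, 4 failures already suffice and power is 0.898. With 17 release and 21 control, 6 are needed and power is 0.751.

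**5. After the change**

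If cells are assigned only at opening, all 42 go to patients whose repair is finished: 21/21, power 0.879 before follow-up losses and 0.812 at 19/19. The required 38 and 42 do not change.

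**The case against.** **Cells need not be lost.** The article nowhere says that a vacated cell or unopened envelope is forfeited. The expectation of 21 operated patients per group and 42 completers can be read as implying replacement, in which case no power is lost. This stands as a limit on the claim: a reader might infer that the cells are certainly spent and 21/21 certainly broken, but the text does not establish that. It does not remove the point, because no section says how a place in a fixed, pre-balanced list would be refilled.

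**The power loss is easily overstated.** A reader might take power at equal arms of 18 and 17, namely 0.77 and 0.72, as the result of 2 to 4 exclusions. Random losses do not fall equally, and imbalance does not in itself cost power with this test: 19 release and 17 control patients give 0.870, against 0.769 for 18/18. The averaged figures are the right ones, and at 2 exclusions they still reach 0.80. The plan also expects few missed visits, apart from the nerve studies, so 4 follow-up losses is a cautious baseline.

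**The two times may be two steps.** A list position could be taken at recruitment and the allocation put into effect at admission. That is a possible reading, but both sentences use the word for randomising, so the text still needs one answer. The difference in counting is confined to refusals between the two dates.

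**Bias is not shown.** Refusal, arthropathy and failed repair all precede opening. If the arm is truly hidden until then, these exclusions cannot depend on it. Selection bias is therefore not an inference the text supports by itself. One caution remains: Study procedure makes the operating surgeon aware of the allocation list, and Randomization/blinding has the surgeon informed on the admission day. Both sit badly with concealment until the repair is done.

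**Conclusion.** The point holds in a limited form. The two sections contradict each other on the time of randomisation, and both times precede exclusions that could be settled before the arm is needed. With no stated rule for reuse of cells, those exclusions become avoidable post-randomisation losses.

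Their size depends on a number that the article does not give. With 4 missed follow-ups, about 2 exclusions can be absorbed before mean power drops below 0.80 (0.803 at 2, 0.757 at 4). With no missed follow-ups, even 4 leave it at 0.843. These figures assume the plan's recovery rates, a two-sided test, losses at random across the list, and no replacement. Provided concealment holds until the repair is finished, the cost is to balance, power and a clear randomised denominator, not to validity. This is a cheap improvement, not a flaw that invalidates the design.

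**What to change.** State one randomisation moment in both Study procedure and Randomization/blinding, for example:

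> *The patient is randomised in the operating room when the nurse opens the next sequentially numbered opaque envelope. This is done after the surgeon has finished the repair and recorded that the existing eligibility and repair criteria of this protocol are met. Patients who leave before that point use no cell and are reported as enrolled but not randomised.*

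Then:

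- delete recruitment and the admission day as times of randomisation;
- delete the statement that the surgeon is informed on the admission day, and the surgeon's access to the allocation list;
- number envelopes by sequence instead of preparing each for a particular patient.

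Tying the trigger to the finished repair, and not only to eligibility seen at arthroscopy, is what covers failed and partial repairs. No eligibility or surgical rule changes. Failed release and re-rupture arise after opening, so this change does not solve them and their handling in the analysis needs its own statement.

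The cost is an amendment and a numbered set of envelopes kept in theatre. The downside is that a few more patients may need to be consented to fill 42 randomised places. Because the trial is recruiting, the change protects only the cells not yet assigned.
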